## Background

### Diabetes and its impact on the community

Diabetes is a systemic disorder resulting in abnormally high blood glucose levels. These elevated levels impact directly and indirectly on every part of the body. Diabetes is the number one cause of end stage renal disease (ESRD), preventable blindness, as well as a major cause of premature heart disease, stroke, limb amputation and preventable hospital admissions[1]. Prevention of type 2 diabetes through primary control programs is society's ultimate goal but current evidence indicates that this goal is failing as rates of diabetes are rising rapidly. For example in the Province of Ontario, prevalence rates of diabetes rose by 69% to 8.8% in the 10 year period ending 2005[2]. Secondary prevention strategies to help reduce the complication rate in this burgeoning population of people with diabetes are desperately needed. Control of blood glucose levels prevents new microvascular disease and has recently been shown to have a legacy effect and is a central focus of diabetes management programs[3], in addition to the significant health benefits of blood pressure and lipid control. The optimal degree of blood glucose normalization has recently come into question. While the ADVANCE study demonstrated a reduction of microvascular but no significant reduction of macrovascular events with normalization of A1c to below 7.0%[4], the ACCORD study, also targeting normalization of A1c below 7.0%, found an elevated mortality and no reduction of cardiovascular events[5].

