We believe that this study protocol has relevance with respect to the development of a new community-based approach to the control of blood glucose. We have recently demonstrated that the Home Care team (which provides supportive care provided in the patient's home by healthcare professionals) of the Battlefords Tribal Council Indian Health Services, can improve blood pressure control using a chronic disease management model for multiple drug therapy[7]. We believe that a chronic disease management model linking the Home Care Team including Diabetes Educators[6] with their clients and the primary care providers to try to bring A1c to 7.0% can improve blood glucose control safely. Combining elements of chronic disease management including provider education, patient education, clinical practice guidelines, decision support and disease measurement is expected to lead to lasting improvements in diabetes management[8]. Use of the Bluetooth enabled glucose meters may be able to enable diabetes intensification in a safe and effective manner, allowing the Home Care team to review their clients with access to their client's self monitored blood glucose results.

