There is now evidence in both type 1 as well as type 2 diabetes that improved glycaemic control will reduce the microvascular complications of diabetes[44]. An epidemiologic analysis of the UKPDS[45] showed that there is no threshold for benefit when it comes to glucose lowering, and that any reduction in A1c is associated with reduced risks for both micro- and macrovascular disease. In their analysis, every 1% decrease in A1c was associated with a 25% reduction in risk for myocardial infarction[45]. The ADVANCE study demonstrated a reduction of microvascular events with normalization of A1c to below 7.0%[4]. The ACCORD study which targeting aggressive normalization of A1c in patients with longstanding diabetes, found an elevated mortality in the intensive group which targeted normalization of blood gluocse[5]. The goal of diabetes intensification in this study is to reduce the risk for the complications of diabetes by controlling blood glucose safely.

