Algorithms developed for diabetes management were developed based on clinical practice guidelines and reviewed with experts in diabetes management. For self monitoring of blood glucose[1], the goal is a minimum of four times daily, two days per week for those on or starting insulin. Medication will be introduced in a stepped fashion for those on diet therapy alone starting with metformin followed by a sulphonylurea (gliclazide, as it is better tolerated in patients that develop kidney disease than others)[53], thiazolidendiones (TZD's) will be added if sulphonylureas have failed. Pioglitazone (Actos) was chosen for use as it is a once daily preparation. This step was added prior to the controversy over rosiglitazone[54]. The algorithm for diabetes intensification to be carried out by the Home Care team was incorporated into a standardized order form for the primary care physician to approve. The study team in partnership with the primary care physician will be responsible for assessing contraindications to the algorithms.

The initiation of insulin is often frightening for patients and a program of education and an algorithm for the introduction of insulin were developed. At all times, the primary care physician will be kept in the loop as part of a management model. After Home Care visits, reports on study letterhead will be faxed or mailed to the primary care physician. In addition, a system of graded alerts developed by the Home Care team including the use of the existing Provincial emergency Health Hotline and medical backup will be used in the study.

The goal of this phase of the program is to facilitate a change of practice to improve diabetes management over the long term. Physicians and the Home Care team need to become integrated and systems developed to do this. The hope is that following the study, patients who require diabetes intensification will be identified by the physician, the Home Care team and possibly by patients themselves. The Primary Care Physician would then initiate the process by signing a completed Home Care referral form for the initiation of intensification of diabetes management. This will initiate a visit by the Home Care team (nurse or dietitian).

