### Analytic procedures and sample size calculation

This is a pilot study that will compare, in a before and after methodology, the intervention of diabetes intensification on the primary response variable of blood glucose level (A1c) measured at baseline and at 6 months. The pilot study will also determine the ability to enroll patients into the study and determine how many are able to maintain an 80% adherence rate to the use of the glucose meter four times daily at least twice weekly. This is also a goal of phase 3 of this study. See Additional file 2 for statistical design considerations.

Initiation of Diabetic Medication Treatment: The goal of Intensification therapy is A1c <7.0%. Patients in the usual care arm will continue to see their primary care physicians. Therapy in the treatment group will be initiated with the goal to bring the fasting plasma glucose ≤ 6 mmol/L and in insulin treated patients, pre-meal glucose concentrations of 4–7 mmol/L.

Safety and Interim Monitoring. Drug therapy may be interrupted at any time during the trial if further evidence for more appropriate drug therapy becomes available. All drugs used in this trial are available in regular clinical practice. Women of child-bearing potential must have a negative urine pregnancy test prior to receiving study medication. Patients will be asked for adverse events from the last visit related to hypoglycemic episodes and these data recorded. In the UKPDS 33 study the rates of major hypoglycemic episodes per year were 0.7% with conventional treatment, 1.0% with chlorpropamide, 1.4% with glibenclamide, and 1.8% with insulin [48,49]. Severe hypoglycemia defined as needing the assistance of another person, or coma, will be tracked, as will diary-recorded instances.

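### As written, adverse-event collection covers only hypoglycaemia, so the pilot could not describe other harms relevant to its goal of safe glucose control

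*Protocol article*

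**What the plan says.** The rule is in the Safety and Interim Monitoring paragraph of Analytic procedures and sample size calculation: "Patients will be asked for adverse events from the last visit related to hypoglycemic episodes and these data recorded". The same paragraph defines one serious event: "Severe hypoglycemia defined as needing the assistance of another person, or coma, will be tracked, as will diary-recorded instances". No other part of the article widens what is recorded.

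Safety is part of the stated purpose. The Background gives the goal as follows: "The goal of diabetes intensification in this study is to reduce the risk for the complications of diabetes by controlling blood glucose safely". It also expresses the belief that a chronic disease management model working "to try to bring A1c to 7.0% can improve blood glucose control safely".

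The Background reports a harm other than hypoglycaemia at a similar target: "the ACCORD study, also targeting normalization of A1c below 7.0%, found an elevated mortality and no reduction of cardiovascular events". The later text on intensification adds that those patients had longstanding diabetes. The goal of intensification in this study is an A1c below 7.0%.

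The section on the Battlefords Tribal Council Indian Health Services says that starting insulin in type 2 diabetes was previously arranged by hospital admission. It gives the project's ultimate goal as a process for starting insulin in the community.

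**The concern.** The sentence is a positive instruction about what to ask and record, so this is more than a detail left to a fuller document. A nurse who follows it would ask about hypoglycaemia and record the answers. A cardiac admission, a death or a drug stopped for another side effect would have no stated place in the data.

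The Discussion presents this work as the foundation for wider use in rural and Northern communities. Readers deciding on that step would want to know what happened to the enrolled subjects besides hypoglycaemia. Admissions matter in particular, because the programme replaces an inpatient route for starting insulin. Events that are not asked about at the time may be hard to recover later.

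**Working it through.** **1. Does any other provision record events on treatment?** The provisions that bear on safety, set side by side:

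| Provision | Where | What it does |
|---|---|---|
| Assessment of contraindications | Phase 2 | Check on suitability for the algorithm |
| Graded alerts, emergency hotline, medical backup | Phase 2 | Care process |
| Endocrinologist review of medication adjustments | Phase 2 | Quality control of care |
| Cardiovascular-renal risk factors | Phase 3 | Initial assessment only |
| Monitoring of doses and compliance | Phase 3 | Guides prescribing; no event or reason for stopping is named |
| Negative pregnancy test | Safety and Interim Monitoring | Check before treatment |
| Interruption of drug therapy | Safety and Interim Monitoring | Triggered by further evidence on drug therapy, not by events in this trial |

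None is a rule to record deaths, admissions or discontinuations for adverse effects. A question put to patients at visits also cannot capture deaths.

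**2. How much information will the recorded category yield?** Inputs: 50 subjects (Phase 1 and Phase 3) and cited major hypoglycaemia rates from 0.7% per year (conventional treatment) to 1.8% per year (insulin). Exposure is an assumption of 1.0 to 1.5 years, because the article gives two durations. The abstract has phase 3 lasting 18 months. The text after Approvals has 18 months from the start of phase 1, which leaves 18 − 3 − 3 = 12 months for phase 3. These need to be reconciled.

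Expected episodes = subjects × rate × years; chance of none = exp(−expected), assuming a Poisson count.

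- Low: 50 × 0.007 × 1.0 = 0.35; chance of none exp(−0.35) = 70%.
- High: 50 × 0.018 × 1.5 = 1.35; chance of none exp(−1.35) = 26%.
- At the 6-month primary time point: 50 × 0.007 × 0.5 = 0.18 to 50 × 0.018 × 0.5 = 0.45.

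All assume that 50 subjects contribute. The article foresees that fewer may enter phase 3 and will not replace them, so these are upper figures for that phase.

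**3. What would wider collection add?** For an event with a true risk of 5% over follow-up (assumed), the chance of at least one among 50 is 1 − 0.95^50 = 92%; at 2% it is 1 − 0.98^50 = 64%. That is useful description for a pilot.

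**4. What would it not add?** The article gives no mortality rate. At an assumed 0.5% to 3% per year, expected deaths run from 50 × 0.005 × 1.0 = 0.25 to 50 × 0.03 × 1.5 = 2.25. In a two-group comparison (two-sided 5%, 80% power, equal allocation, all assumed), deaths needed = 4 × (1.96 + 0.84)² / (ln HR)². This gives about 945, 191 and 66 for hazard ratios of 1.2, 1.5 and 2.0. No change in collection makes this pilot informative about excess mortality.

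**The case against.** The strongest reply is that emphasis is being read as exclusion. The sentence does not say that only hypoglycaemia is recorded. The case report forms and additional files are not shown, and reporting of deaths and serious events is often set out there. This stands as a limit: the restriction is certain only for the article. It does not remove the point, because if the forms collect more, the article misdescribes the plan and should be corrected.

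A second reply is that all the drugs are in regular clinical use, so focused collection is defensible in a small pilot. That is a fair reason not to build an elaborate safety system. It is weaker against a few fields on death, admission and discontinuation.

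Three stronger readings are tempting, and the documents do not support them.

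- A reader might infer that the trial makes a safety claim it cannot support because of this restriction. Safe control is stated as a goal and a belief, the primary outcome is A1c at 6 months, and the sample is too small for inference on mortality even with complete collection.
- A reader might infer a known thiazolidinedione risk that goes uncollected, from the remark on that drug step: "This step was added prior to the controversy over rosiglitazone". The algorithm uses pioglitazone, the controversy concerns another drug of the class, and the article does not say what it was about.
- A reader might infer that most serious events will fall outside hypoglycaemia. The article gives no rate for other serious events against which to judge this.

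The mortality finding also needs its context: the article places it in longstanding diabetes, and cites another trial with A1c below 7.0% that found fewer microvascular events.

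**Conclusion.** The point holds in limited form. The article's recording rule names only hypoglycaemia, and nothing else shown plans to record deaths, admissions or discontinuations for adverse effects. As written, the pilot could not describe non-hypoglycaemic harms relevant to its goal of safe control. The category it does record is likely to be sparse for major episodes: about 0.35 to 1.35 expected, given 50 subjects, the cited rates and an assumed 1.0 to 1.5 years. The loss is descriptive information, not a test of safety. This should be changed, but it does not undermine the A1c comparison. The conclusion assumes that the unseen forms follow the article's sentence.

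**What to change.** Reword the sentence under Safety and Interim Monitoring so that, at each existing visit, patients are asked about all adverse events since the last visit, hypoglycaemia included. Add case report form fields for every death, every hospital admission with its reason, and every drug discontinuation for an adverse effect. Apply them to all enrolled subjects, including those followed as control when the primary care physician declines the algorithm and those followed by intention to treat. Report these descriptively beside hypoglycaemia, with no inference on mortality.

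If collection stays restricted, say so and confine any safety statement to hypoglycaemia. If the forms already collect more, correct the sentence to match.

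The cost is one reworded question, a few form fields and slightly more nurse recording time at visits already planned. No treatment rule changes.

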### Rates of use of insulin and hypoglycemia, evidence from clinical trials

Studies of glycaemic control in people with type 1[46] and type 2[44] diabetes have shown improvements in complications such as the progression of kidney, eye and heart disease. Achieving control of blood glucose requires adherence to lifestyle changes as well as titration of medications, including the initiation of insulin therapy and the titration of the insulin dose. The intensive treatment group of the STENO-2 study led to over 50% being started on insulin with an average dose of 62 units per day[47]. Of interest, a greater proportion of the usual care group was started on insulin and there was a trend to higher doses. The glycaemic target in the intensive arm of the STENO-2 study was an A1c of 6.5%, compared to about 7.5% in the control arm. Despite lower blood glucose levels attained in the intensive treatment group, there were fewer major hypoglycemic complications (eg. impaired consciousness which required help from another person) in the intensive treatment compared to the control group (just under 1% vs. 2% per patient year respectively)[47]. In the UKPDS 33 study the rates of major hypoglycemic episodes per year were also relatively low, 0.7% with conventional treatment, 1.0% with chlorpropamide, 1.4% with glibenclamide, and 1.8% with insulin[48,49]. Fear of the complications of insulin therapy, particularly hypoglycemia, by both patients and health care workers, is one of the major barriers to implementing intensification of diabetes management. The ability to monitor blood glucose levels remotely in people who are having their diabetes medications adjusted may go a long way to providing the same kind of safety net for diabetes management that was the rationale for managing diabetes in the hospital setting years ago.

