The ability to accurately monitor blood glucose results with self monitoring of blood glucose (SMBG) is pivotal to the success of managing and controlling blood glucose levels in people with diabetes on insulin. Glucose meters in current use require the user to record the displayed result into a logbook along with the timing of the reading. This allows cumulative readings to be analyzed for patterns. Barriers to health care workers receiving accurate logbooks include the ability and willingness of the person using the glucose meter to record the results accurately and to bring the logbook with them to appointments with health care providers. Evidence provided by glucose meters with memories has demonstrated that the recording of results into logbooks may not be accurate[52], even when glucose meters users know that their device is also recording the levels. Furthermore, health care providers only get access to the information in the logbook or that stored within the glucose meter during patient or client visits. This may lead to prolonged episodes of dysglycaemia before the client can receive medical attention. Bluetooth enabled glucose meters facilitate the downloading of the results to a secure electronic format available to health care providers via a web interface. This may help to eliminate the effects of geography and will allow the potential for more frequent health care monitoring of SMBG. The health care team can arrange for more frequent monitoring during titrations of drug therapies or the initiation of insulin. Patients with questions about their management will be able to initiate a health care provider review of their results by phone-call without generating a visit.

The ultimate goal of the DreamTel project is to develop a process for initiating insulin therapy in the community setting including intensification of diabetes management in a culturally appropriate manner. If successful, the legacy of the project will be a change in medical practice in the community with the introduction of a chronic disease management model for type 2 diabetes management, where primary care physicians can consult with the Home and Community Care team for initiation of insulin therapy in the community as well as intensification of diabetes therapy.

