Another objective for the first three months of use is to compare data from three different sources; data transmitted by the device and stored on the web site, data stored on the device itself and the patient's log book, noting discordant values. Data is to be presented as the proportion of results recorded accurately. The frequency of monitoring based on data from the electronic output is to be assessed for the entire period.

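### Non-severe hypoglycaemia is ascertained only from patient report and diaries; a predefined low-reading measure from the meter data already collected should be added alongside them

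*Protocol article*

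**What the plan says.** The Safety and Interim Monitoring paragraph (Protocol article, under Analytic procedures and sample size calculation) names the sources for hypoglycaemia. The first is questioning at visits: "Patients will be asked for adverse events from the last visit related to hypoglycemic episodes and these data recorded". The second sentence covers severe events and diaries: "Severe hypoglycemia defined as needing the assistance of another person, or coma, will be tracked, as will diary-recorded instances". No glucose threshold is given, no meter or web reading is named as a source, and the route by which severe events are tracked is not stated. The same paragraph quotes yearly rates of major episodes from a large type 2 diabetes trial, from 0.7% with conventional treatment to 1.8% with insulin.

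Elsewhere the article explains why electronic readings are wanted. The section on the Battlefords health services says "the recording of results into logbooks may not be accurate[52], even when glucose meters users know that their device is also recording the levels", and then that "Bluetooth enabled glucose meters facilitate the downloading of the results to a secure electronic format available to health care providers via a web interface". The section on insulin use and hypoglycaemia offers "The ability to monitor blood glucose levels remotely in people who are having their diabetes medications adjusted" as a safety net like the one hospital management once provided. The stated goal of intensification is to "reduce the risk for the complications of diabetes by controlling blood glucose safely".

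The Phase 1 section compares "data transmitted by the device and stored on the web site, data stored on the device itself" with the patient's log book. It names two results: the proportion of values recorded accurately, and how often patients test. Low glucose is not among them.

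**The concern.** Safety of intensification in the community, including starting insulin, is one of the questions that the project sets out to address, and hypoglycaemia is the hazard that it singles out. The stated ascertainment nevertheless leaves out the instrument under study. Part of it rests on a diary, most naturally read as the logbook whose accuracy the article doubts.

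If severe events are too rare to be informative, the safety picture depends on non-severe low glucose. Those events are then known only through what patients remember or write down. A low count could mean few episodes or few reports, and the plan as stated has no second source to tell these apart. It also states no low-glucose measure for Phase 1, the period before intensification, to set against Phase 3 in what is otherwise a before-and-after design.

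**Working it through.** The article states no expected event count or precision for hypoglycaemia, so there is no figure to reproduce. The checks ask how much severe events could show, and what the readings could add.

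**Inputs**
- Subjects: 50 (Phase 1 and Phase 3 sections). Phase 3 shortfalls are not replaced.
- Rates: 0.7% to 1.8% per year (Safety and Interim Monitoring), treated here as events per patient-year.
- Exposure to intensification: the paragraphs after Approvals count 18 months from the start of Phase 1. The Abstract gives Phases 1 and 2 three months each, so 18 − 3 − 3 = 12 months. The Abstract also gives Phase 3 itself 18 months. Both lengths are shown.
- Testing goal: four times daily on two days a week for those on or starting insulin (Phase 2 section), with an 80% adherence threshold.

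**Severe events.** Expected = subjects × rate × years; chance of none = exp(−expected).

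| Subjects | Years | Rate | Expected | Chance of none |
|---|---|---|---|---|
| 50 | 1.0 | 0.7% | 0.35 | 0.70 |
| 50 | 1.0 | 1.8% | 0.90 | 0.41 |
| 50 | 1.5 | 0.7% | 0.53 | 0.59 |
| 50 | 1.5 | 1.8% | 1.35 | 0.26 |
| 25 (assumed shortfall) | 1.0 | 1.8% | 0.45 | 0.64 |
| 25 (assumed shortfall) | 1.5 | 1.8% | 0.68 | 0.51 |

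If no severe event occurred, the one-sided 95% upper limit would be −ln(0.05)/patient-years:
- 50 patient-years: 2.996/50 = 6.0 per 100 patient-years.
- 75 patient-years: 2.996/75 = 4.0 per 100 patient-years.

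Both limits exceed twice the highest cited rate (2 × 1.8 = 3.6), so a count of zero would not show a rate as low as those cited.

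**What the readings offer.** The goal is 4 × 2 = 8 readings a week, or 8 × 26 = 208 per subject over 26 weeks. For 50 subjects that is 50 × 208 = 10,400 at full adherence and 0.8 × 10,400 = 8,320 at 80%. These figures apply the insulin-user goal to everyone, so they are generous.

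**What the readings miss.** Planned tests fall on 2 of 7 days. Suppose that tests are random in time and a low episode lasts 30 to 120 minutes (both assumptions). The share of episodes that coincide with a planned test is then about 8 × 0.5/168 = 2.4% to 8 × 2/168 = 9.5%. Testing prompted by symptoms would raise this.

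**The case against.** Several stronger readings are tempting, and the document does not support them.

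- A reader might infer that the protocol calls its own sources inaccurate. It doubts only the copying of glucose values into logbooks, and in hedged terms. It says nothing against patients' accounts at visits, and it does not state that the diary is the logbook.
- A reader might infer that the meter would measure hypoglycaemia directly and could displace patient report. Readings exist only when the patient tests, and many episodes would fall between tests. Severe events are defined by assistance or coma, which no meter can establish.
- A reader might infer that the protocol plans to claim safety by comparison with the quoted rates. It plans no such comparison; the rates stand as context. That a 50-subject pilot cannot estimate a rate of 1% to 2% a year is a limit of any such pilot, not an error in this one.
- A reader might credit all 50 subjects with 18 months at the insulin rate and full testing, giving 50 × 1.5 = 75 patient-years and 8 × 78 × 50 = 31,200 readings. These are ceilings. Insulin is the last step of the algorithm, and Phase 3 takes only those who reach the testing threshold.

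The electronic data also already serve safety in care. Providers see readings on a portal, the educators and the endocrinologist can review them together weekly, and graded alerts are planned. These are care processes, however. The article does not say that alerts or low readings are counted as study data, or what triggers an alert.

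Finally, analytic detail may lie in Additional file 2, which is not shown. That is a fair limit: one cannot say that low readings will never be analysed. The point does not rest on missing detail, though. The article itself states how hypoglycaemia is ascertained, and the stated choice can be improved.

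**Conclusion.** The point holds as a worthwhile improvement to the stated ascertainment. It is not a contradiction that undermines the trial, and the primary A1c outcome is unaffected.

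Severe events will probably number none or one: the expected count is at most 1.35 under the longest exposure and highest cited rate, and 0.35 to 0.90 over 12 months. What the pilot learns about hypoglycaemia will therefore come mainly from non-severe lows, for which the article names only report and diary. The transmitted readings would give an independent, timed, though partial, second source.

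This rests on the cited rates applying to these subjects, on all 50 entering Phase 3 (fewer would lower the counts), and on Poisson events. The coverage of 2% to 10% of episodes rests on assumed durations and random test times. It is given only to show why the measure must supplement reports.

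**What to change.** 1. Add a predefined low-glucose measure from meter-stored and transmitted readings, alongside reported and diary events and not in place of them. The investigators should fix the threshold before the data are examined. Report low readings per subject and per 100 readings, in Phase 1 and in Phase 3, excluding tests flagged as validation runs or another person's sample.
2. Show testing frequency beside the measure in each phase. Subjects who start insulin are expected to test to a set goal, and symptoms may prompt extra tests, so a change in low readings can reflect a change in testing.
3. State the source for severe events, report them with an exact Poisson interval and the patient-years at risk, and say that the pilot cannot establish a rate comparable with the cited trials.

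The cost is small: the readings are already transmitted and stored, and subjects are already taught to flag tests that are not their own. It needs a short added analysis and a few sentences, with no new visits or data collection. The one downside is that the measure depends on when patients test, which item 2 makes visible.
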